#### Secondary outcomes

2.4.2

Several secondary outcomes will be examined in this study, including full remission, body-shape dissatisfaction, therapeutic alliance, clinical impairment, health-related quality of life, attrition, and an economic evaluation using the costs associated with psychiatric illness, and treatment costs to assess cost-effectiveness and cost-utility, as described in detail below. The timing of secondary outcome measurements is outlined in **Table 2**. Baseline scores, demographic variables, and BMI will be examined as moderators.

**Table 2 T2:** Timing of assessments and outcome measurements.

	Timepoints				
Outcome measure	T0: Baseline	T1: Mid-treatment	T2: End of treatment	T3: 20 weeks post-treatment	T4: 40 weeks post-treatment
Demographics	x				
EDE-Q	x	x	x	x	x
EDE	x	x	x	x	
TIC-P	x		x	x	x
EQ-5D-5L	x		x		
WAI		x	x		
CIA	x	x	x	x	x
BSQ	x	x	x	x	x

EDE-Q, Eating Disorder Examination- Questionnaire (EDE-Q); EDE, Eating Disorder Examination; TIC-P, Questionnaire on Costs associated with Psychiatric Illness; EQ-5D-5L, Health-Related Quality of Life questionnaire; WAI, Working Alliance Inventory; CIA, Clinical Impairment Assessment; BSQ, Body Shape Questionnaire.

##### Full remission

2.4.2.1

Full remission will be assessed using the Eating Disorder Examination (EDE; 45) interview, with a combined measure of no binge-eating episodes in the previous 28 days, and eating disorder pathology below clinical cut-off of 2.8 (46). The EDE interview is a semi-structured interview assessing eating disorder pathology during the last 28 days, including binge eating. The scale consists of four subscales on dietary restraint, eating concern, weight concern and shape concern, and is measured on a 7-point Likert scale (47). The EDE has good internal consistency, discriminative validity, and reliability (48), and has been translated and validated in Dutch (49). The Eating Disorders Examination Questionnaire (EDE-Q; 50, 51) will be used at the 40-week post-treatment assessment. The EDE-Q is a 36-item questionnaire based on the EDE and the global score is calculated as the sum of the four subscales scores, divided by four (the number of subscales).

##### Body shape dissatisfaction

2.4.2.2

Body shape dissatisfaction will be examined using the Body Shape Questionnaire (BSQ; 47). The BSQ contains 34 questions on a 6-point Likert scale ranging from “never” to “always”. The questionnaire has demonstrated good concurrent and discriminant validity, internal consistency, and test-retest reliability (52, 53).

##### Therapeutic alliance

2.4.2.3

Therapeutic alliance, or the working relationship a patient has with a therapist, will be measured using Dutch version of the Working Alliance Inventory (WAI; 54, 55) to examine differences in therapeutic alliance between GSH and TAU, given therapeutic alliance can be impacted in online therapy (56). The WAI is a self-reported questionnaire with 36 items scored on a 7-point Likert scale examining the alliance between the patient and therapist. For the purposes of this study, only the patient’s perspective will be assessed. The questionnaire has three dimensions: Bonds, Tasks, and Goals. The Dutch version has been validated by (55).

##### Clinical impairment

2.4.2.4

Clinical impairment refers to the psychosocial impairment suffered by patients as a direct result of their binge-eating disorder (Fairburn, 2008). The Clinical Impairment Assessment (CIA; 57) will be used to examine impairment secondary to eating disorder psychopathology, as the CIA differentiates between eating disorder pathology and secondary impairment due to the eating disorder. The questionnaire is self-reported and consists of 16 items with personal, social, and cognitive subscales, and is rated on a 4-point Likert scale.

##### Health-related quality of life

2.4.2.5

Health-related quality of life will be measured using the Dutch version of the Euroqol EQ-5D-5L, a five-dimension, five level measure of health status (58). The scale has five dimensions with one item per dimension on mobility, self-care, usual activities, pain and discomfort, and anxiety/depression. Each item is rated on a 5-point scale with: no problems, slight problems, moderate problems, severe problems and extreme problems.

##### Attrition

2.4.2.6

Attrition bias will be measured to determine whether participants in either group are more likely to have incomplete assessments or prematurely dropout of treatment. Attrition will be measured by the total amount of non-response and missing data (59), and dropout will be measured by the total number of participants that formally withdraw from treatment.

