#### Moderators

2.4.3

Baseline scores, demographic variables, and BMI will be examined as moderators. Baseline scores, including the number of objective binges and eating disorder severity will be examined given prior research suggests that more severe BED pathology at baseline predicts less improvement in BED pathology at the end of CBT-E treatment (66, 67), and may also predict greater treatment dropout (21). Demographics, such as age, gender, and level of education, will be examined as possible moderators. Lastly, BMI, calculated by dividing the participant’s weight in kilograms by the square of height in meters (kg/m2), will be examined as a moderator.

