#### Sample size and power estimation

2.5.1

The primary objective of the proposed study is to determine whether GSH is noninferior to TAU in efficacy. It is expected that both groups will have a reduction in the number of binge-eating days, and GSH is expected to be noninferior compared to TAU in the reduction of binge-eating days in the previous 28 days at the end of treatment.

To calculate the sample size for this noninferiority trial, the significance level was set at *α* = 0.05, power was aimed at 80%, and the noninferiority margin (*Δ*) was set to 1 (*SD* = 2.4) binge-eating day (68) in the previous 28 days between groups. With these assumptions, *n* = 144 (*n* = 72 per arm) participants will be needed to determine noninferiority. The noninferiority margin and standard deviation are based on noninferiority margins from prior studies examining online treatments to reduce eating disorder behaviors (68, 69) and clinical experts on BED treatment outcomes. Efficacy studies of CBT-E (70) and internet-based guided self-help for BED (68) report a 20% dropout; therefore, 20% more participants will be included to compensate for dropout. The sample size corrected for dropout is *N* = 180 (*n* = 90 per arm); therefore 180 participants will be randomized. This sample size calculation was performed using the R package ‘SampleSize4ClinicalTrials’ (71–73) based on a continuous outcome, noninferiority design.

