## Anticipated results

3

It is expected that at the end of treatment, the difference in reduction of binge-eating days between web-based GSH CBT-E and TAU CBT-E is within the noninferiority margin (Δ) of 1 binge-eating day (68). Regarding secondary outcomes, it is expected that there will be no difference in the rate of full remission, clinical impairment, or reduction in body shape dissatisfaction between groups. However, it is expected that more severe binge-eating pathology at the start of treatment will predict a weaker treatment response, regardless of condition (80). In addition, the economic evaluation is expected to demonstrate that GSH is more cost-effective than TAU, while having similar cost-utility (31, 81). Therapeutic alliance is expected to be the similar between groups (82). Attrition rate is expected to be approximately 20% in both conditions (68, 83). As for moderators, it is expected that baseline scores will moderate the treatment effect; for example, it is expected that participants with a greater number of objective binges at baseline will demonstrate a slower response to treatment (84). Demographic information is expected to have no effect on the reduction of binge-eating days. Lastly, is expected that BMI will have a small moderating effect on binge-eating reduction, such that participants with a greater baseline BMI will have a weaker response to treatment, regardless of group.

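### The attrition-bias measure compares only how much is missing in each arm, so it detects differential attrition but not whether the people lost differ between arms

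*Protocol article*

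**What the plan says.** Section 2.4.2.6 (Attrition) gives the purpose: "Attrition bias will be measured to determine whether participants in either group are more likely to have incomplete assessments or prematurely dropout of treatment". It then gives the metric: "Attrition will be measured by the total amount of non-response and missing data". Dropout is counted separately, as the number of formal withdrawals from treatment.

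Three other places bear on this:

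- Section 3 (Anticipated results): "Attrition rate is expected to be approximately 20% in both conditions".
- Section 2.4.3 (Moderators) says that more severe pathology at baseline predicts less improvement and "may also predict greater treatment dropout".
- Section 2.5.3 (Statistical analyses) plans a general linear mixed model for binge-eating days and, in view of the anticipated dropout, intention-to-treat analysis with multiple imputation.

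**The concern.** The section names attrition bias, but what it sets out to compare is the amount of loss in each arm. Equal amounts are neither necessary nor sufficient for an unbiased contrast. What matters is how the missing participants differ from the observed ones, and whether that difference is the same in both arms.

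The plan's own expectations make this relevant. It expects equal attrition, in which case the stated comparison carries no information about bias. It also expects that sicker patients may drop out more, so it has a reason to think that loss is selective. In a noninferiority trial the unfavourable case is that guided self-help (GSH) participants who do poorly go missing while losses under treatment as usual (TAU) are unrelated to outcome. The observed contrast then moves towards noninferiority while the two attrition figures agree.

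**Working it through.** **Inputs from section 2.5.1.** "the significance level was set at *α* = 0.05"; power 80%; the margin "was set to 1 (*SD* = 2.4) binge-eating day"; 20% dropout. The true difference is taken as 0. The article does not state sidedness.

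**Reproducing the sample size.** With one-sided 0.05, n per arm = 2 × 2.4² × (1.645 + 0.842)² / 1² ≈ 71.3, rounded up to 72, so 144 in total. Then 144 / 0.8 = 180, or 90 per arm. Both figures reproduce. One-sided 0.025 would need 91 per arm and does not. At 20% loss, 18 of 90 are missing and 72 observed in each arm, and the standard error of the difference is 2.4 × √(2/72) = 0.40 day.

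**Bias at equal attrition.** Let d be the proportion missing, equal in both arms, and let the gap in an arm be the mean binge-eating days at T2 of missing participants minus that of observed ones. An arm's full mean is its observed mean plus d × gap. So the observed contrast (GSH minus TAU) differs from the full one by −d × (gap in GSH − gap in TAU). With d = 0.2, the shift is 0.2 times the difference in gaps.

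The documents do not give the gaps, so the first column is an assumption. The last column is Φ(−1.645 + shift / 0.40), the chance of declaring noninferiority in a completer comparison when the true deficit equals the margin.

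| Difference in gaps (days) | Difference in attrition rates | Shift towards noninferiority (days) | False noninferiority, completers |
|---|---|---|---|
| 0 | 0 | 0 | 5% |
| 1 | 0 | 0.2 | 13% |
| 2 | 0 | 0.4 | 26% |
| 3 | 0 | 0.6 | 44% |
| 5 | 0 | 1.0 | 80% |

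The second column is zero throughout. That is the point: the stated measure does not move while the shift does.

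**What the planned analysis would remove.** Two simulated cases bracket this.

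- *Loss in GSH driven by mid-treatment (T1) status; TAU loss at random; T1–T2 correlation 0.6; 18 of 90 missing per arm; mean gap about 1.4 days.* Completers show a shift of about 0.28 day and 17% to 18.5% false noninferiority. An estimate that includes T1 leaves at most about 0.01 day; in the run that tracked the error rate, false noninferiority was 5.8%.
- *Loss in GSH driven by the unseen T2 outcome itself, correlation 0.3, 0.5 or 0.7 between loss and outcome.* Completers show about 0.25, 0.41 and 0.59 day. Imputing on one earlier measure correlated 0.5 with the outcome leaves about 0.19, 0.33 and 0.46 day. With a correlation of 0.7, about 0.12, 0.22 and 0.33 day remain.

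**What a comparison of missing with observed participants would show.** In the first case, comparing T1 values within the GSH arm flags the selection in 97% to 99% of simulated trials. The contrast of that gap between arms, which is what bears on bias, flags it in about 79%. Both figures assume that every participant has T1 data.

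**The case against.** The strongest reply is that nothing in the efficacy analysis depends on section 2.4.2.6. Attrition is a secondary outcome, and comparing retention between a low-contact and a higher-contact treatment is legitimate in itself. The mixed model and multiple imputation deal with missing data, and when loss depends on T1 status they remove nearly all the bias if T1 is included. This stands. The completer error rates above are therefore not error rates of the planned analysis.

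A reader might infer more from the text than it supports:

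- *That the plan treats equal attrition as proof of no bias.* It sets no threshold, test or decision rule and never says so. The weakness is that its measure cannot answer the question it names.
- *That selective loss will use up much of the 1-day margin.* No gap size has a source in the documents. Section 2.4.3 says that severity may predict dropout, not that it does so differently by arm. If loss is equally selective in both arms, the shift is zero.
- *That missed visits are summed over timepoints.* The word total allows this, but section 3 speaks of a rate, and the definition cites a source not available here. The text does not settle it, which is a reason to name the visit and no more.

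It can also be said that tables of missing versus observed participants and the choice of imputation variables belong in an analysis plan. That is so where an article is silent. Here it states a measure and calls it attrition bias, so the measure can be judged as stated.

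**Conclusion.** The concern holds in limited form. Section 2.4.2.6 specifies a measure of differential attrition under the name of attrition bias. With the roughly equal 20% loss that the plan expects, it would show no difference whether or not the participants lost differ between arms.

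The consequence is confined to how attrition is interpreted and to what is learned for the missing-data model. The size of any bias in the primary contrast is unknown. It is 0.2 times an unsourced difference in gaps for completers, less after a model that carries the variables related to loss, and zero if selection is alike in both arms. Loss that depends on the unobserved T2 outcome would be only partly removed. The sample size is unaffected. This is a worthwhile, inexpensive improvement and not a flaw that invalidates the analysis.

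**What to change.** 1. Call the section 2.4.2.6 comparison differential attrition. Report it as the proportion of randomised participants per arm without the T2 binge-eating-day outcome, with each other visit shown separately. This can be set directly against the 20% used for the sample size.
2. Assess attrition bias by comparing participants with and without T2 data, within each arm and between arms, on baseline binge-eating days, baseline EDE global score, BMI and, where available, T1 binge-eating days. Read sizes rather than p-values. State that similar attrition rates are not evidence of no bias.
3. Include these variables in the imputation model.
4. Add a delta or tipping-point analysis against the 1-day margin for loss that depends on the unobserved outcome, which step 2 cannot detect.

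The cost is revised wording, one extra table and one extra sensitivity analysis. No new data are needed: Table 2 already schedules the EDE and EDE-Q at baseline and T1, and BMI is already used for stratification. The drawback is imprecision, since about 18 participants per arm would be missing and those lost before T1 contribute baseline data only.

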##### Cost associated with a psychiatric illness

2.4.2.7

The costs associated with psychiatric illness will be measured using the Dutch version (60) of the questionnaire on healthcare consumption and productivity loss in patients with a psychiatric disorder (TiC-P) (61). The questionnaire for adults is composed of three parts and considers the cost of medical and mental health care, company doctors, social services, allied health care, residential care, alternative care, home help and support, addiction care, medication, and diet. The TiC-P will be used for the cost-effectiveness and cost-utility analysis to measure health care use and productivity loss.

##### Cost of treatment

2.4.2.8

The cost of treatment will be determined from a healthcare perspective. For each patient, the cost of treatment will be calculated by multiplying standard Dutch cost prices (62) by the total number of minutes spent on direct patient contact. The time horizon for this study will be 52 and 60 weeks; therefore, no discounting for future costs will be applied.

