#### Treatment as usual CBT-E

2.3.2

Treatment as usual CBT-E is the focused version of CBT-E, as it is indicated for patients with BED and exclusively addresses eating disorder pathology and is more effective than the broad version, which addresses external mechanisms (14). During the COVID-19 pandemic, face-to-face CBT-E treatment for BED could no longer continue, and consequently, video conferencing CBT-E was introduced as TAU at Novarum to ensure continued patient care. In this study, TAU CBT-E will be delivered through video conferencing over 20 sessions, each 50 minutes in length. The treatment follows the same structure and duration as face-to-face CBT-E; however, it is offered completely remotely. Video conferencing CBT-E has been as effective as face-to-face treatment (27, 31, 43, 44). Participants receiving TAU CBT-E will be required to monitor their eating behaviors, weigh themselves regularly, evaluate their progress, find alternative activities to binge eating, improve their problem-solving skills, plan for relapse prevention, and learn ways to cope through setbacks (36).

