#### Web-based guided self-help CBT-E

2.3.3

Web-based guided self-help CBT-E is an adapted and brief version of the focused form of CBT-E. The treatment is based on the guided self-help book *Overcoming Binge Eating* (36) is also available in Dutch *Overwin je eetbuien, waarom je te veel eet en hoe je daar mee kunt stoppen* (43), and is being built into a Dutch online application (Karify by Avinty). Before beginning web-based GSH, participants will be required to read part 1 of *Overcoming Binge Eating* (44). Treatment will be offered completely remotely using the web-based application, and focus on the same CBT-E principles as in TAU: monitoring eating behaviors, regular weighing, evaluating progress, finding alternative activities to binge eating, and improving problem-solving skills (36). Participants will receive weekly scripted feedback from a therapist during 12 phone sessions of 20 minutes. During these calls, therapists will review past assignments and discuss next steps in treatment.

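### Treatment cost is defined by direct-contact minutes alone, so the cost of the web application that delivers guided self-help enters neither ICER

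*Protocol article*

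**What the plan says.** All references are to the protocol article.

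- **Costing rule (2.4.2.8, Cost of treatment).** "The cost of treatment will be determined from a healthcare perspective", and each patient's cost is obtained by "multiplying standard Dutch cost prices (62) by the total number of minutes spent on direct patient contact". No other treatment input is named.
- **GSH delivery (2.3.3).** The book-based programme "is being built into a Dutch online application (Karify by Avinty"), and treatment is given entirely through that application. Before starting, "participants will be required to read part 1 of" the self-help book. Therapist contact is by telephone: "Participants will receive weekly scripted feedback from a therapist during 12 phone sessions of 20 minutes". During those calls, "therapists will review past assignments and discuss next steps in treatment".
- **TAU delivery (2.3.2).** "TAU CBT-E will be delivered through video conferencing over 20 sessions, each 50 minutes in length".
- **Other costs (2.4.2.7).** The TiC-P "considers the cost of medical and mental health care", along with other services, medication and diet. Treatment software is not among the items listed.
- **Use of the cost (2.5.3).** The difference in costs, GSH minus TAU, is the numerator of both incremental cost-effectiveness ratios (ICERs): the one per binge-eating day and the one per QALY.

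**The concern.** GSH is cheaper by design because an application and self-study take over part of what a therapist does in TAU. A rule that prices only therapist contact measures the input that GSH reduces and gives no price to the application that partly replaces it. This is a complete formula stated in the article, so the omission is not simply detail left to a fuller document. If the formula is followed as written, a delivery cost specific to GSH goes uncounted.

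The credibility of the cost difference is at stake. The trial expects the two arms to be similar in effect, so the ICER denominators may be small. An error of P in the numerator moves an ICER by P divided by the effect difference. For example, an effect difference of half a binge-eating day would move it by 2P. Section 3 anticipates that GSH will be the more cost-effective arm, and section 2.1 promises a complete economic evaluation.

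**Working it through.** The article states no treatment cost, unit price or cost difference, so there is no figure to reproduce. The check starts from the planned sessions.

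**Step 1: planned contact minutes (2.3.2 and 2.3.3).**
- GSH: 12 × 20 = 240 minutes
- TAU: 20 × 50 = 1,000 minutes
- Gap: 1,000 − 240 = 760 minutes; GSH is 240/1,000 = 24% of TAU

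Minutes actually delivered will vary with attendance; these are the planned values.

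**Step 2: saving under the rule and with the omitted terms.** Let r be the price per contact minute, P the per-patient platform cost (plus any provider-paid material) in GSH over and above that in TAU, and m the off-contact therapist minutes per session, taken as equal in both arms.
- Saving under the rule = 760r
- Full saving = r[(1,000 + 20m) − (240 + 12m)] − P = r(760 + 8m) − P
- Error in the rule = 760r − full saving = P − 8mr

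With m = 0 the rule overstates the saving by exactly P. With P = 0 it understates the saving by 8m minutes. The two cancel when P = 8mr; for example, m = 10 and r = €1 give P = €80.

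**Step 3: size under assumed ranges.** None of r, P or m is in the article. The assumptions are r = €1–€2, P = €0–€200 and m = 0–15. Errors are percentages of the full saving.

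| Case | Rule saving | Full saving | Error |
|---|---|---|---|
| r = €2, P = €25, m = 0 | €1,520 | €1,495 | +1.7% |
| r = €1, P = €100, m = 0 | €760 | €660 | +15.2% |
| r = €1, P = €200, m = 0 | €760 | €560 | +35.7% |
| r = €1, P = 0, m = 5 | €760 | €800 | −5.0% |
| r = €1, P = 0, m = 10 | €760 | €840 | −9.5% |
| r = €1, P = 0, m = 15 | €760 | €880 | −13.6% |
| r = €1, P = €100, m = 10 | €760 | €740 | +2.7% |

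Over the whole grid the error runs from about −14% to +36%. The smallest full saving is €560, so GSH remains cheaper on treatment cost throughout. With m = 0, P would have to reach 760r, that is €760 to €1,520 per patient, to remove the saving.

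**The case against.** **The unit price may already carry overhead.** The standard Dutch price comes from a cited source that is not shown, and it may include indirect time and overhead. This stands for off-contact therapist time, and adding such time to a loaded price would count it twice. It does not answer the platform point. A loading proportional to contact minutes gives TAU 1,000/240 = 4.2 times the overhead of GSH, and it cannot represent the cost of an application that does not scale with contact minutes.

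**TAU may have a platform cost too.** Section 2.1 calls both treatments web-based, and TAU runs by video conferencing. This stands. Only the difference in platform cost between the arms biases the comparison, and the article gives neither cost. Nor does it say that the application carries a per-patient charge.

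**The book may not be a provider cost.** This stands. The payer is not stated, and a book bought by the patient falls outside a healthcare perspective.

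**GSH-specific off-call work.** A reader might infer that therapists review assignments outside the calls and that this time goes uncosted in GSH only. The article does not support that reading: it places both the feedback and the assignment review inside the telephone sessions, so they are already contact minutes.

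**Double counting through the TiC-P.** Because the TiC-P covers mental health care, a reader might infer that study sessions will be counted twice. The article presents illness-related cost and treatment cost as separate components, and nothing says that sessions enter both. How the two are kept apart is detail that an article commonly leaves to the full plan.

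**Conclusion.** The point holds for the delivery platform. The stated rule has no term for the application through which GSH is given, and the listed TiC-P items do not supply one. Any per-patient platform cost that the provider bears for GSH alone overstates the GSH saving by that amount in both ICER numerators.

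The net bias in the cost difference is not established in direction or size. P is not given, TAU may have its own platform cost, and off-contact time shared equally per session would push the other way. The range of −14% to +36% rests entirely on assumed prices and minutes.

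A reader might go further and infer that the rule settles the cost-effectiveness answer in advance. The article does not support that. Health care use from the TiC-P and the measured effects also feed the economic analyses, one of the omissions works against GSH, and the sign of the treatment-cost difference does not change anywhere in the assumed ranges. The economic evaluation is a secondary outcome, and what is in doubt is the size of the saving and of the ICERs. The correction is still worth making, because the rule is explicit and the remedy is cheap.

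**What to change.** In section 2.4.2.8, define treatment cost per patient, in each arm, as the sum of:

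1. direct-contact minutes multiplied by the standard unit price;
2. the per-patient cost of the delivery platform, meaning the application in GSH and video conferencing in TAU;
3. any treatment materials paid for by the provider.

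State whether the standard unit price already includes indirect therapist time. Only if it does not, add a standard off-contact time per session in both arms. Keep the contact-only cost as a sensitivity analysis, so that readers can see how much the platform term matters.

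The change needs a few prices from the centre's records and, at most, one standard time per session. It does not alter trial conduct or the assessments. The possible downside for the sponsor is that the GSH saving may look smaller.
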